### Abscission or termination of allocated interventions

Any subject who does not complete the observation period as specified in the protocol should be recorded as a case of abscission unless the patient’s symptoms disappeared before treatment.

The following are possible reasons for abscission or termination:
Poor drug compliance will be considered if the medication compliance test result is less than 80%. Compliance = (total number of pills taken / prescribed pills) × 100%.Consumption of drugs that are not permitted during the clinical study, including other hormones and immunosuppressants not mentioned in the trial such as cyclophosphamide, mycophenolate, and so on.Incomplete information due to failure to complete the entire course of treatment for any reason.Serious adverse events or complications making it inappropriate to continue the trial and resulting in the discontinuation of treatment.

The following measures should be taken:
Attempt to contact the subject to ask for an explanation for abscission or termination and record the last time the patient took the medicine and completed an assessment.In the case of withdrawal from the test due to anaphylaxis, adverse reactions, or ineffective treatment, appropriate treatment measures should be actively taken.An abscission case form should be completed that explains the cause in detail.Statistical analyses, including analyses of intention-to-treat (ITT) and safety set (SS), will be performed on abscission cases as appropriate. If the abscission rate exceeds 5%, the reason for abscission will be explained in detail.

Termination of study cases may occur for the following reasons:
In children with light type HSPN, if the 24-h urinary protein quantity reaches the heavy type (35–50 mg/kg) during the second week of treatment, the patient may be considered an invalid case and potentially be randomly regrouped as heavy type HSPN; it should be noted that for cases invalid in light type, the outcome will be included in the intention-to-treat analysis instead of excluding these patients. For participants who have already been re-randomized as heavy type, the data will be analyzed separately. Sensitivity analyses with and without these particular patients who may have crossed over between interventions will also be performed.In patients with serious adverse events or no therapeutic effects after 4 weeks of treatment, the trial should be discontinued at the doctor’s discretion; they are no longer followed and the outcome is not included in the analysis.Patients who are unwilling or unable to continue the clinical trial for any reason.

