Diagnostic criteria	2 main symptoms of blood heat (or 1 main symptom + 2 secondary symptoms) + 1 main symptom of blood stasis

**Table 3 Tab3:** Observation protocol to be followed during treatment and follow-up

Observed indicator/week		Treatment stage (week)								Follow-up stage (week)								
		0	1	2	4	6	8	10	12	16	20	24	28	32	36	40	44	48
Main	24-h urinary protein quantity	×	×	×	×	×	×	×	×	×	×	×	×	×	×	×	×	×
Secondary	Urine red blood cells	×	×	×	×	×	×	×	×	×	×	×	×	×	×	×	×	×
Security	Routine blood tests	×	×	×	×	×	×	×	×	×	×	×	×	×	×	×	×	×
	Hepatic and renal function	×	×	×	×		×		×		×		×		×		×	×

2.Follow-up stage (12–48 weeks).

The 12-week treatment stage will be followed by a 36-week follow-up stage. The main aim of the follow-up is to monitor a series of laboratory indicators and determine the disease recurrence rate. The details are presented in Table 2.

In patients who meet the clinical control standards after 12 weeks of treatment, medication will be stopped and the patients will begin follow-up. The clinical control standards mean that RBC counts and 24-h protein in urine are at normal levels, and urine routine examinations are negative for protein and occult blood. For those patients who do not meet the clinical control standards by 12 weeks, other treatment options could be appropriately selected in the professional judgment of the clinicians. The clinicians who are evaluating the follow-up laboratory results (and determining whether there is a relapse or whether the patient has reached clinical control standards) are not blinded to the patient’s treatment assignment. The criteria for efficacy evaluation are presented in Table 4.

**Table 4 Tab4:** Criteria for efficacy evaluation

Primary outcome	Clinical control rate	Significant efficiency	Effective rate	Ineffective rate
PRO in urine	Negative	PRO decreased by 2+	PRO decreased by +	PRO decreased less than +
	24-h urinary protein quantity is normal	24-h urinary protein quantity reduced > 50%	24-h urinary protein quantity reduced between 30 and 50%	24-h urinary protein quantity reduced < 30% or no change
RBC in urine	U-OB: negative	U-OB: RBC reduction ≥ ++/HP	U-OB: RBC reduction ≥ +/HP	U-OB: no improvement or aggravation in RBC
	RBC ≤ 5/HP	RBC count decreased By > 50%	RBC count decreased between 30 and 50%	RBC count decreased < 30% or no change
Total therapeutic effect	Meet all these requirements	Meet all these requirements	Meet all these requirements	Meet all these requirements

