*RBC* red blood cells, *U-OB* urine occult blood, *PRO* Urinary protein, *HP* high power microscope

If the disease relapses during follow-up, the details of the recurrence will be recorded and the appropriate treatment administered in a timely manner while follow-up is completed. Other treatment options are available to patients who do not meet the clinical control standards, and it will be necessary to record any decisions and proceed with the follow-up stage.

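### Children stopped for serious adverse events or lack of effect leave follow-up, so later urine protein and safety visits are lost for reasons tied to outcome

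*Protocol article*

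**What the plan says.** The list of reasons for terminating study cases, under Abscission or termination of allocated interventions, has this trigger: "In patients with serious adverse events or no therapeutic effects after 4 weeks of treatment". The consequence is that "the trial should be discontinued at the doctor’s discretion; they are no longer followed".

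Earlier in that section, the reasons for abscission include "Serious adverse events or complications making it inappropriate to continue the trial and resulting in the discontinuation of treatment". For abscission cases, staff are to "record the last time the patient took the medicine and completed an assessment", and "Statistical analyses, including analyses of intention-to-treat (ITT) and safety set (SS), will be performed on abscission cases as appropriate".

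The follow-up part of the Intervention section handles other treatment failures differently:
- At the end of the treatment stage: "For those patients who do not meet the clinical control standards by 12 weeks, other treatment options could be appropriately selected". For these children "it will be necessary to record any decisions and proceed with the follow-up stage".
- For a child who relapses, the recurrence is recorded and "the appropriate treatment administered in a timely manner while follow-up is completed".

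The Outcomes section makes 24-h urinary protein the primary indicator and compares the arms at each of 17 nodes to week 48. It schedules 11 liver and kidney tests, also to week 48. The Blinding section describes the trial as open-label.

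**The concern.** Stopping study drug and stopping observation are separate decisions, and the termination rule merges them. Both triggers arise after randomization. Lack of effect is itself a statement about the outcome, and a serious adverse event is a safety result. Missing visits that follow from either are therefore unlikely to be missing at random. The doctor who uses the discretion knows the arm, so the threshold for stopping could also differ between arms.

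Two things are at stake. First, the node-by-node comparison of urine protein after a stop would rest on a selected set of children. Second, recovery from a serious event, and any later blood, liver or kidney abnormality, would go unseen in the children for whom it matters most. This bears on a stated aim of the trial, which is to provide a reference dose of tripterygium glycosides for children.

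**Working it through.** **1. Reproduce the plan's visit counts (Table 3 and Outcomes).**
- Urine protein: weeks 0, 1, 2, 4, 6, 8, 10, 12 (8 visits) plus weeks 16, 20, 24, 28, 32, 36, 40, 44, 48 (9 visits). 8 + 9 = 17, as stated.
- Liver and kidney function: weeks 0, 1, 2, 4, 8, 12 (6) plus weeks 20, 28, 36, 44, 48 (5). 6 + 5 = 11, as stated.

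**2. Count the visits lost per stopped child.** Lost share = scheduled visits after the stop ÷ all scheduled visits.

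| Last visit before the stop | Urine protein lost | Liver/kidney lost |
|---|---|---|
| Week 4 | 13/17 = 76% | 7/11 = 64% |
| Week 8 | 11/17 = 65% | 6/11 = 55% |

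Table 3 schedules routine blood tests at the same 17 weeks as urine protein, so their loss is also 13/17 and 11/17.

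**3. See whether anything in the article restores these visits.**
- Recording the last dose and last assessment fixes the date of the final observation. It adds none after it.
- Analysing abscission cases by intention to treat and in the safety set, as appropriate, says who is counted. It cannot supply measurements that sites were told not to take.
- The section on adverse events requires the triggering event to be recorded and serious events to be reported within 24 h. That secures the event, not the scheduled tests afterwards.
- The increase of about 20% in the sample size allows for missed visits. It protects precision, not against selective loss.

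**4. Compare with the rule for other failures.**

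| Child | Stage | Follow-up |
|---|---|---|
| Serious adverse event, or no effect after 4 weeks, stopped at discretion | Treatment stage | Ends |
| Not at clinical control at week 12 | End of treatment stage | Continues to week 48 |
| Relapse | Follow-up stage | Completed |

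The overlap is the true non-responder. If stopped after week 4, that child leaves the data. If kept on to week 12, the child is followed to week 48. The doctor's discretion decides which.

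**5. Size of bias.** This would need the share stopped in each arm and the later course of those children. The article gives neither, so no figure follows from it.

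**The case against.** **The contrast is partial.** The week-12 rule applies at a later stage and to a wider group. By Table 4, a child whose 24-h protein fell by more than half can still be short of clinical control. A reader might infer that the protocol treats the same children in opposite ways. The text supports that only for a non-responder who could fall under either rule. What remains is that visits after a change of treatment were considered workable.

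**The size is unknown.** A reader might infer a definite shift in the treatment difference. The documents do not support one. The control rates in the sample size section are week-4 figures, and the Outcomes section says that the earlier week-12 difference was not significant, so they should not be carried to later nodes. A shift calculated by taking stopped children out of the denominator would also measure something else, namely the separate statement in the same sentence that their outcome is left out of the analysis. If stopped children were kept and counted as not controlled, a binary control rate would need no later visit from them. That does not help the primary indicator, which is a measured quantity at each node, or the safety tests.

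**Not every safety stop is drug toxicity.** This is correct. The trigger is a serious adverse event, and its relation to the drug is assessed separately. The loss is still linked to safety.

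**It is late.** The Trial status section puts the trial in its statistical stage. That limits the remedy but does not make the rule sound. Nor can an unseen fuller protocol or analysis plan excuse it: the article states the rule outright, and no analysis can recover visits that were never made.

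**Conclusion.** The point holds as a flaw in the follow-up rule. As written, a child stopped at week 4 contributes nothing to 13 of 17 urine protein nodes and 7 of 11 liver and kidney tests. The loss follows from outcome or safety, at the discretion of an unblinded doctor. Later comparisons and safety follow-up are therefore weighted towards children who tolerated and responded to treatment.

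The visit counts rest only on the published schedule and on sites following the rule literally. How far the trial's result is affected, and in which direction, depends on how many children were stopped in each arm and how they fared afterwards. The article does not say, so no claim is made that either arm is favoured.

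**What to change.** Strike the clause that takes these children out of follow-up. Word the rule as a stop of study drug, for example: a child with a serious adverse event, or without therapeutic effect after 4 weeks, may have study drug discontinued at the doctor's discretion; further treatment is recorded, and the Table 3 assessments continue to week 48. This matches what the Intervention section already provides after relapse or failure to reach clinical control.

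Because the trial is in its statistical stage, the part that can be used now is to keep in the analysis every post-stop visit that was in fact collected.

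The cost is the visits already on the schedule for the stopped children: at most 13 urine protein visits and 7 liver and kidney tests for a child stopped at week 4. Visits already missed are gone, and neither the rewording nor the analysis can bring them back.

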### Blinding

Because TCM syndrome differentiation is needed during the research process, this is an open-label trial. To improve patient compliance in patients who come to the Chinese Medicine Hospital for TCM treatment, a regular group will be treated with Chinese medicine granule simulation drugs (placebo).

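### Children whom an unblinded doctor stops for a serious adverse event or for no effect after 4 weeks are dropped from follow-up and from the analysis, in conflict with the intention-to-treat handling stated in the same section

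*Protocol article*

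**What the plan says.** The section on abscission or termination of allocated interventions holds three rules that bear on this point.

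- **Termination, second item.** "In patients with serious adverse events or no therapeutic effects after 4 weeks of treatment, the trial should be discontinued" at the doctor's discretion, and "they are no longer followed and the outcome is not included in the analysis". The rule gives no threshold for absence of effect.
- **Abscission.** The listed reasons include "Serious adverse events or complications making it inappropriate to continue the trial and resulting in the discontinuation of treatment". For abscission cases the section says: "Statistical analyses, including analyses of intention-to-treat (ITT) and safety set (SS), will be performed on abscission cases as appropriate".
- **Termination, first item.** For light-type children whose proteinuria reaches the heavy range in week 2, "the outcome will be included in the intention-to-treat analysis instead of excluding these patients". The sensitivity analyses promised there concern only these re-randomised children.

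The Intervention section adds that children who miss the clinical control standards have their treatment decisions recorded and go on into the follow-up stage.

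On blinding, the Blinding section states: "Because TCM syndrome differentiation is needed during the research process, this is an open-label trial". The Intervention section says that the clinicians who judge control and relapse from follow-up results "are not blinded to the patient’s treatment assignment".

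**The concern.** The second termination item decides who is analysed by what happened after randomisation. A child stopped for no effect is a treatment failure by definition, and the efficacy analysis in the Statistical analysis section is a comparison of clinical control. Removing that child takes a known non-responder out of the denominator. The decision is discretionary, has no stated criterion, and is made by a doctor who knows the arm.

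Two things are at stake. The reported control rates no longer describe the randomised children. If doctors stop children at different rates in the two arms, the comparison is also biased. On safety, ending follow-up after a serious adverse event loses the later blood, liver and kidney results that Table 3 schedules to week 48, in a trial meant to evaluate safety.

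**Working it through.** **1. The rules side by side.**

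| Child | Rule | Handling |
|---|---|---|
| Treatment discontinued for a serious adverse event | Abscission list | Intention-to-treat and safety-set analysis, as appropriate |
| Stopped for a serious adverse event, or for no effect after 4 weeks | Termination, second item | Not followed, not analysed |
| Light type, worsens to heavy range in week 2 | Termination, first item | Kept in intention-to-treat |
| Control standards not met | Intervention section | Follow-up continues |

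The first two rows can apply to the same child and give opposite instructions. The last two rows concern other children. They show a different approach to poor outcomes but do not contradict the second row.

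**2. Inputs.** From the Sample size calculation section: 500 children at 2:1, hence 333 and 167; week-4 planning rates of 48.6% (TCM) and 35.7% (control), a difference of 48.6 − 35.7 = 12.9 points. The calculated total of 405 is not needed here. The share removed is not given. *Assumptions:* 5% to 20% of an arm removed, all of them non-responders.

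**3. Effect on one arm.** If a share d is removed and none of those removed had reached control, the analysed rate is p/(1−d).

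**4. No true difference, p = 40% in both arms (assumed).** False-positive rates are for a two-sided 5% two-proportion z-test, by normal approximation, with 333(1−d) and 167(1−d) children analysed.

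| Removed, TCM/control | Analysed rates | Spurious difference (TCM − control) | False-positive rate |
|---|---|---|---|
| 10%/10% | 0.40/0.90 = 44.4% in both | 0 | 5% |
| 15%/5% | 0.40/0.85 = 47.1% vs 0.40/0.95 = 42.1% | +5.0 points | 17% |
| 5%/15% | 42.1% vs 47.1% | −5.0 points | 17% |
| 20%/5% | 0.40/0.80 = 50.0% vs 42.1% | +7.9 points | 35% |
| 5%/20% | 42.1% vs 50.0% | −7.9 points | 34% |

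With the plan's own control rate of 35.7% in both arms, 15%/5% gives about 15% and 20%/5% about 29%.

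**5. Planning rates taken as true (12.9 points when failures are counted).**

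| Removed, TCM/control | Analysed rates | Apparent difference |
|---|---|---|
| 10%/10% | 54.0% vs 39.7% | 14.3 points |
| 20%/5% | 0.486/0.80 = 60.75% vs 0.357/0.95 = 37.6% | 23.2 points |
| 5%/20% | 0.486/0.95 = 51.2% vs 0.357/0.80 = 44.6% | 6.5 points |

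**The case against.** The strongest reply is that the rule is narrower than it looks and that its effect cannot be sized.

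- **Scope.** A reader might infer that treatment failures in general are removed. The text does not support that. Only children actually discontinued under this item are dropped. Children not controlled at week 12 stay in follow-up, worsened light-type children stay in intention-to-treat, and Table 4 has grades between ineffective and controlled. This stands.
- **Direction.** A reader might infer that the exclusion favours TCM. No removal rate is given for either arm, and reversed removal favours control. Equal removal leaves the type I error at 5%. This stands.
- **Serious adverse events.** These children need not be non-responders, and the Background reports no serious adverse reactions in the earlier 172-case trial. The arithmetic therefore fits the no-effect group best. This stands.
- **Cox model.** A reader might infer informative censoring. The text says the outcome is left out, which means these children are absent from the Cox model, not censored in it.
- **Week 4.** The rule applies after 4 weeks, so the week-4 visit may already be recorded, and the excluded outcome might mean later outcomes only. The wording does not say so.
- **Hedged wording.** The abscission rule applies as appropriate, and the explicit non-blinding sentence concerns follow-up results. The first softens the conflict but does not withdraw the exclusion. For the 4-week decision, lack of blinding follows from the open-label design.

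None of this restores the excluded children to the analysis.

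**Conclusion.** The exclusion is wrong as written and must be changed. It is an explicit instruction that conflicts with the abscission rule in the same section, so it is not a detail left to the analysis plan. The analysed set is no longer the randomised set, whatever the numbers turn out to be.

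The size is conditional. With 5% to 20% of each arm removed and only non-responders among them, the planned 12.9-point difference could appear as anything from 6.5 to 23.2 points. Under no true difference at 40%, the false-positive rate runs from 5% with equal removal to about 35% with 20% against 5%, in favour of whichever arm loses more children. That stopping differs between the arms is plausible in an open-label trial, but the documents do not show it.

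**What to change.** Delete "they are no longer followed and the outcome is not included in the analysis" and reconcile the abscission rule, both termination items and the follow-up rule in the Intervention section. Then state:

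- Every randomised child is analysed in the allocated arm.
- A child stopped for lack of effect or a serious adverse event before reaching control counts as control not reached from that point in the logistic analysis. In the Cox model the child stays in the risk set, event-free, to week 48.
- Control events and visit data recorded before the stop are kept.
- All these children are in the safety set, and any data collected after the stop are used.
- The analysis without them is reported only as a sensitivity analysis.

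The cost of the analysis rule is wording, since coding non-response needs no data after the stop. Follow-up to week 48 can be kept only for children not yet lost: the Trial status section says the trial is already in its statistical stage. Reported control rates will be lower than under the present rule, by an amount that depends on how many children were stopped. This takes no position on when treatment should stop.

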### Adverse events and serious adverse events

Every adverse events (AE) that occur during the trial will be faithfully recorded and evaluated for a possible association between AEs and the experimental drugs in accordance with the Guidelines for Clinical Research of New Chinese Medicine Drugs (Trial), a standard designated by the pharmaceutical adverse reaction monitoring center of the Ministry of Health. Necessary measures will be immediately taken to protect the safety of the patients and to determine whether to stop observation.

If any adverse events occur during the study, the investigator should take necessary measures according to the patient’s condition with time. In the case of mild adverse events not affecting the subject’s health, no special treatment or symptomatic treatment is required; for moderate adverse events, the trial should be discontinued and targeted treatment should be given to the subjects.

When serious adverse events (SAEs) occur during a trial, it is extremely important to report them to the responsible units involved in the project, including the Ethics Commission, the Data and Safety Monitoring Board, and the Food and Drug Administration (FDA), within 24 h. Severe adverse events will endanger the lives of subjects, and the clinical trials should be stopped immediately and emergency treatment should be given. The units in charge of the project and the participating units should make common emergency plans for dangerous conditions such as allergic reaction, cardiac arrest, respiratory failure, heart failure, and so on.

